#### Contamination Bias

To minimize contamination bias, the intervention program will be conducted outside their follow-up clinic time. The intervention program will be conducted at the seminar room of the designated hospitals. Participants are strongly encouraged not to disclose the program materials or discuss them with other caregivers of patients with TBI outside the program.

#### Blinding

The method of blinding in RCT is used to ensure that there are no differences in the way in which each group is assessed or managed and therefore minimize bias. In this study, only the principal investigator is aware of the treatment allocated to the participants.

### Statistical Analysis

Data analysis will be performed using SPSS software (version 24.0; IBM Corp). Descriptive statistics will be used to describe the characteristics of participants. Continuous data will be reported as means and SDs or as medians and IQRs. Categorical data will be reported as percentages and frequencies. The comparison of the means between the 2 groups will be performed using a paired samples 2-tailed *t* test. In addition, 1-way ANOVA and repeated measure ANOVA will be conducted to identify any significant differences in mean scores of emotional distress (BDI), caregiver’s needs (Family Needs Questionnaire [FNQ]), burden of care (Caregiver Strain Index [CSI]), and life satisfaction (Satisfaction With Life Scale [SWLS]) before the intervention, after the intervention, at 3-month follow-up, and at 6-month follow-up between the intervention and control groups. Multivariate regression analysis will be used to determine the predictors of intervention outcomes.

The intention-to-treat analysis will be performed accordingly. Assumptions of normality and homogeneity of variance will be conducted and adjusted where necessary.

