## Methods

### Study Design

This is a 2-arm, single-blinded, randomized controlled trial (RCT). All participants will be randomly assigned to the intervention group or control group. Only the investigators will be aware of the treatment allocation.

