### Participants

A total of 100 participants were recruited for this study. Of the 100 participants, 50 (50%) were randomly assigned to the intervention and control groups, respectively. All caregivers of patients with TBI who attend follow-up with patients with TBI at the Neuro Rehabilitation outpatient clinic of HRC and HSB were screened for eligibility to participate in this study.

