### Inclusion and Exclusion Criteria

To be eligible, caregivers of patients with TBI must be citizens or permanent residents of Malaysia and be aged ≥18 years, regardless of their race, ethnicity, and sex. The participants must be able to read or write in Bahasa Malaysia or English. The caregivers can be the parents, spouses, siblings, sons or daughters, or relatives of the patients with TBI. Only 1 caregiver per patient with TBI can be recruited for the program. Time since injury for the patient with TBI must be >3 months and time spent on caring for the patients must be at least 2 hours per day. All types of injury severity were included. However, paid caregivers were excluded.

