### Sample Size Estimation

Sample size estimation is based on the formula for clinical superiority trial [51]:

N=2x (Z_1–α_ + Z_1–β_)^2^ × S^2^ / (δ–δ_0_).

The sample size is calculated with 80% power (Z_1–β_=0.845) at a significance level (α) of .05, with 95% CI (Z_1–α_=1.96), 25% dropout rate, and medium size effect of 0.60. The parameters used in the formula will be based on a previous study [45], including δ^2^=9.355 (pooled SD) and depression (Beck Depression Inventory [BDI] score) δ–δ_0_=5.86 (mean difference). According to the calculation, a total of 50 participants per arm will be needed for this study.

The parameter used to compute the prevalence of caregivers of patients with TBI was taken from the paper titled “Life satisfaction and strain among informal caregivers of patients with traumatic brain injury in Malaysia” [25].

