### Allocation

#### Allocation Sequence Generation

Methods of random allocation are used to ensure that all study participants have the same chance of allocation to the treatment or control group. Caregivers of patients with TBI who are eligible and consent to participate will be number coded before randomization. A simple random sampling method using computer-generated random sampling will be used to assign participants to the intervention group or control group. The procedure would be performed by following the 1:1 allocation format. Randomization will be performed by the principal investigator. All participants will have equal chance of being assigned to the intervention or control group.

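### The t test named for comparing the two arms is a paired-samples test, but the arms are unmatched, independent caregivers; for PANAS, a primary scale, no other between-arm mean comparison is named

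*Protocol article*

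**What the plan says.** Statistical Analysis (protocol article) gives the two-group comparison in one sentence: "The comparison of the means between the 2 groups will be performed using a paired samples 2-tailed" *t* test. The next sentence adds: "In addition, 1-way ANOVA and repeated measure ANOVA will be conducted to identify any significant differences in mean scores". It lists BDI, FNQ, CSI and SWLS at the four assessment times and says that the contrast is between the intervention and control groups. PANAS is not listed. The section calls none of these tests primary. It also commits to an intention-to-treat analysis.

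The design sections describe independent arms:
- Study Design: "All participants will be randomly assigned to the intervention group or control group".
- Allocation Sequence Generation: "A simple random sampling method using computer-generated random sampling will be used to assign participants to the intervention group or control group", and "The procedure would be performed by following the 1:1 allocation format".
- Inclusion and Exclusion Criteria: "Only 1 caregiver per patient with TBI can be recruited for the program".
- Participants: "Of the 100 participants, 50 (50%) were randomly assigned to the intervention and control groups, respectively".

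Primary Outcomes defines emotional distress by two scales, BDI and PANAS.

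**The concern.** A paired *t* test needs a real link between each member of one arm and one member of the other. The article describes no matching. Simple randomization creates no link, and the one-caregiver rule means that two relatives of the same patient cannot sit in opposite arms.

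The sentence can be carried out in two ways, and neither is a sound comparison of the arms:
- **Across arms.** Row *i* of one arm is paired with row *i* of the other. The result then depends on how the file is sorted. A caregiver with data is discarded if the person on the same row of the other arm is missing, which conflicts with the intention-to-treat commitment.
- **Within arm.** The test assesses change from baseline in one group. It does not estimate the difference between BIFI and usual care.

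The stake is greatest for PANAS. It is one of the two primary scales, and this is the only between-group comparison of means that the article names for it.

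**Working it through.** **Inputs.** All are from Sample Size Estimation and Participants: pooled SD 9.355, BDI mean difference 5.86, Z values 1.96 and 0.845, "at a significance level (α) of .05", dropout 25%, 50 per arm.

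**1. The plan's own sample size.** Read 9.355 as the SD (it is labelled so, though printed with a squared symbol) and square the denominator:

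n = 2 × (1.96 + 0.845)² × 9.355² / 5.86² = 2 × 7.868 × 87.516 / 34.340 = 40.1 per arm; 40.1 × 1.25 = 50.1.

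This reproduces the stated 50. The factor 2 with a pooled SD is the variance of a difference between two independent means. The formula has no within-pair correlation term. The trial was therefore sized for independent groups.

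**2. Degrees of freedom.** Independent test: 2 × 50 − 2 = 98. Paired test: 50 − 1 = 49.

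**3. Average power with complete arbitrary pairs.** Standardized difference 5.86 / 9.355 = 0.626. Noncentrality 0.626 × √(m/2), two-sided α = 0.05, noncentral *t*. Here 38 is 50 × 0.75 = 37.5, rounded up.

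| m per arm | Independent | Paired, arbitrary |
|---|---|---|
| 50 | 87.3% | 86.7% |
| 38 | 76.9% | 75.8% |

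The loss is about one percentage point.

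**4. Power if incomplete pairs are lost.** Assume that pairs are fixed at entry and that the 25% dropout is independent between the two members. Complete pairs: 50 × 0.75 × 0.75 = 28.1. With 28 pairs the power is about 62%. The documents state neither assumption.

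**5. Dependence on row order.** In one simulated data set with 50 per arm, SD 9.355 in each arm and an observed difference of 4.0, the independent test gives P = 0.035. Over 10,000 arbitrary pairings of the same data, the paired P ran from 0.003 to 0.088 and was below 0.05 in 81%. With an observed difference of 3.7 the independent P is 0.051, and 41% of pairings fell below 0.05. With 5.86 (independent P = 0.002) every pairing was below 0.05. These are illustrations. The order matters when the result lies near the threshold.

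**6. Type I error.** If pairing is unrelated to outcome, the paired differences are independent with mean zero under the null, so the average error rate stays nominal. A simulation of 40,000 null trials gave 5.1%.

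**7. Which tests cover which scale.**

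| Scale | Role | Paired *t* test | ANOVAs between groups |
|---|---|---|---|
| BDI | Primary | Yes | Listed |
| PANAS | Primary | Yes | Not listed |
| CSI, FNQ, SWLS | Secondary | Yes | Listed |

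The *t* test sentence names no scale, so it is read here as applying to all of them.

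**The case against.** The strongest reply is that this is a slip of one word in a plan that otherwise treats the arms as separate groups. The sample size formula does so, and the ANOVA sentence explicitly contrasts intervention with control. With two arms at one visit, a 1-way ANOVA is the equal-variance independent *t* test (F = t²), and a group-by-time repeated measures ANOVA can also compare the arms. For BDI, CSI, FNQ and SWLS this stands: the article already names a valid between-arm test. It does not stand for PANAS.

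A reader might infer more than the documents support:
- **That the trial's main comparison is invalid.** No analysis is labelled primary, and the paired test is not the only one named for BDI.
- **That power drops to 62%.** This needs the pairing and dropout assumptions in step 4. With complete pairs the loss is about one point.
- **That false positives are inflated.** Across arms they are not, on average. Within an arm, natural improvement could produce significance with no BIFI effect, but how often depends on a natural fall in BDI that the article does not give. At n = 50, assumed falls of 1 to 5 points with baseline correlations of 0.3 to 0.7 give about 10% to nearly 100%, so no single figure is defensible.
- **That the 1-way ANOVA should be removed.** It would be wrong across repeated visits, where it treats one person's scores as independent. At a single visit it is a correct comparison of the arms.

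A wording slip is plausible, but intent cannot be read from the text, and the sentence says that the comparison is between the groups.

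**Conclusion.** The point holds. A stated analysis contradicts the article's own design and sample size calculation. This is a wrong statement rather than a detail left to a fuller document. The harm is an arbitrary result near the significance threshold and the loss of caregivers whose invented partner is missing, not a large average loss of power or an inflated error rate. The four scales in the ANOVA sentence have a valid alternative, although nothing says which test governs. PANAS has none among the named comparisons of means. The power figures rest on reading 9.355 as the SD, on the planned 5.86-point difference, and on pairs unrelated to outcome.

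**What to change.** In Statistical Analysis:
1. For the between-arm comparison of BDI and PANAS, replace the paired-samples test with an independent-samples 2-tailed *t* test. A baseline-adjusted comparison would also serve, since baseline scores are already collected.
2. Limit any paired *t* test to describing within-arm change, with no claim of effectiveness drawn from it.
3. Keep the 1-way ANOVA only for comparing the arms at a single visit, not across repeated visits.

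The sample size does not change, because it already assumes independent groups. No new data are needed. The cost is a wording change and a re-run of the analysis, which the article reports as being in its final stage. Anticipated Findings already mentions a significant fall in distress against control without naming the test, so the report should say which test produced it.

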### Aims of This Study

This study aims to assess the effectiveness of BIFI in reducing emotional distress and burden of care, besides fulfilling the needs and increasing the life satisfaction of caregivers of patients with TBI in selected hospitals.

The hypotheses of this study are as follows:

There is a significant association between the sociodemographic and clinical characteristics of patients with TBI and the emotional distress, burden of care, needs, and life satisfaction of caregivers of patients with TBI.There is a significant difference in the mean scores of caregivers’ emotional distress, burden of care, needs, and life satisfaction between the intervention and control groups before the intervention, after the intervention, at 3-month follow-up, and at 6-month follow-up.The sociodemographic and clinical characteristics of the patients are predictors of the intervention outcomes.

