### Data Collection and Time Frame

Recruitment for potential participants was conducted by the rehabilitation physicians at both hospitals, who are also the coinvestigators of the study. They screened for potential participants among the caregivers of patients with TBI who attend regular rehabilitation therapy and follow-up at their clinics. These caregivers were then invited to participate in this study. If the caregiver was interested in learning more about the study, they were led to another room, where the investigator explained the study in great detail and answered any questions that the caregivers had. At this stage, a patient information sheet about the nature of the study was provided to the potential participants.

The investigator then left the room for 10 to 15 minutes to allow the caregiver to read the information and to think about whether they would like to participate in the study. If they expressed interest in participating, they were asked to sign the consent form before completing the questionnaire. The same questionnaire used at baseline will be distributed immediately after the intervention, at 3-month follow-up, and at 6-month follow-up. The questionnaire will take approximately 30 to 40 minutes to complete. Data collection was performed between December 2018 and December 2020.

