### Ethical Considerations

#### Approval

This study has been reviewed by the Medical Research and Ethics Committee Malaysia, Ministry of Health Malaysia (NMRR 18-2253-42951). Ethics approval has been obtained from the National Medical Research Register (NMRR-18-2253-42951-IIR) for the study to be conducted at the Ministry of Health settings. Please refer to Multimedia Appendices 1 and 2 for further details of Research Ethics comments and review. The approval letter was received on December 19, 2018. The recruitment period started in December 2018 and was completed on December 18, 2020.

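### Baseline is analysed as one of four outcome times instead of as a covariate, which dilutes the arm effect; the named ANOVA also conflicts with intention to treat unless missing scores are imputed

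*Protocol article*

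**What the plan says.** The Statistical Analysis section of the protocol article plans that "1-way ANOVA and repeated measure ANOVA will be conducted to identify any significant differences in mean scores of emotional distress (BDI"), caregiver needs, burden and life satisfaction, compared "before the intervention, after the intervention, at 3-month follow-up, and at 6-month follow-up between the intervention and control groups". Hypothesis 2, under Aims of This Study, predicts a significant difference in mean scores "between the intervention and control groups before the intervention, after the intervention, at 3-month follow-up, and at 6-month follow-up". Neither place names an adjustment for baseline in the comparison of the arms.

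The same section says "The intention-to-treat analysis will be performed accordingly". It does not say how a missing score is handled. Sample Size Estimation allows for 25% dropout.

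On timing, Data Collection and Time Frame says "Data collection was performed between December 2018 and December 2020", and the Approval section says "The recruitment period started in December 2018 and was completed on December 18, 2020". The last outcome assessment, T4, is the 6-month follow-up.

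**The concern.** There are two linked problems and one separate one.

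- **Baseline as an outcome.** The first score is taken before the intervention has been delivered. In a randomized trial the expected arm difference at that time is zero, so a hypothesis that it is significant can be supported only by chance. In the four-level ANOVA the zero is averaged into the group main effect and shrinks it. Used as a covariate, the same score would instead remove between-person variance.
- **Complete cases.** Classical repeated-measures ANOVA uses a person only if all four scores are present. With 25% dropout expected, that leaves about three quarters of the caregivers unless scores are imputed, and the comparison is then no longer one of the groups as randomized.
- **Dates.** If recruitment and data collection both stopped in December 2020, the last recruits could not have a 6-month score.

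At stake are the sensitivity of the primary BDI comparison, the set of caregivers it describes, and what can be claimed at 6 months.

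**Working it through.** **Inputs from Sample Size Estimation:** SD 9.355, BDI difference 5.86 (5.86 / 9.355 = 0.626 SD), z values 1.96 and 0.845, 25% dropout, 50 per arm. **Assumed, not in the documents:** equal variance and equal correlation ρ between any two visits, with ρ = 0.3, 0.5 or 0.7; an effect of 5.86 at each of T2, T3 and T4; dropout completely at random.

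**1. The plan's own figure.** 2 × (1.96 + 0.845)² × 9.355² / 5.86² = 40.1 per arm, and 40.1 × 1.25 = 50.1. The stated 50 is reproduced. It rests on a comparison of two means at a single time.

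**2. What the group main effect estimates.** The arm differences at the four times are 0, 5.86, 5.86 and 5.86. Their mean is 3 × 5.86 / 4 = 4.40.

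**3. Completers.** 50 × 0.75 = 37.5 per arm. For an unadjusted comparison at one time, 0.626 × √(37.5 / 2) = 2.71, and 2.71 − 1.96 = 0.75, so power is about 77%. At 50 per arm it is about 88%.

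**4. Closed form at 37.5 per arm, ρ = 0.5.**
- Group main effect over four levels: SD of a person's mean = 9.355 × √((1 + 3ρ)/4) = 7.40; standard error = 7.40 × √(2/37.5) = 1.71; 4.40 / 1.71 = 2.57; power about 72%.
- Group-by-time: noncentrality = (37.5/2) × 0.75 × 5.86² / (9.355² × (1 − ρ)) = 11.0 on 3 and 219 degrees of freedom; power about 80%.
- Baseline-adjusted mean of T2–T4: residual SD = 9.355 × √((1 + 2ρ)/3 − ρ²) = 6.04; standard error = 1.39; 5.86 / 1.39 = 4.2; power about 98–99%.

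**5. Simulation** (3,000 trials per scenario, 50 per arm, 25% dropout), which agrees with the closed form:

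| Analysis, constant effect | ρ = 0.3 | ρ = 0.5 | ρ = 0.7 |
|---|---|---|---|
| Four-level ANOVA, completers, group main effect | 83% | 70% | 64% |
| Four-level ANOVA, completers, group-by-time | 63% | 80% | 96% |
| Baseline-adjusted mean of T2–T4, completers | 98% | 98% | 99.8% |
| Baseline-adjusted mean of available T2–T4 scores | 99% | 99% | 99.9% |

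If the effect falls by a third of its starting size at each visit (5.86, 3.91, 1.95), the figures for ρ = 0.3 / 0.5 / 0.7 are: group main effect 51% / 41% / 33%, group-by-time 50% / 64% / 88%, baseline-adjusted on available scores 85% / 88% / 96%.

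**6. Where the loss arises.** The third and fourth rows differ little, while both ANOVA rows are lower. Most of the loss comes from using baseline as an outcome level, and little from losing incomplete cases. Under no effect (run at ρ = 0.5), with random dropout, the ANOVA tests rejected in about 5% of trials, so their type I error is sound.

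**7. Non-random dropout, as an illustration.** If caregivers in the intervention arm with worse T2 scores leave more often (assumed logit slope 0.5 to 1.0 per SD, 25% dropout per arm), the completers' difference at T4 becomes 6.2 to 7.3 against a true 5.86.

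**The case against.** Several stronger readings are tempting, and the documents do not support them.

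- **That every caregiver with a missed visit is dropped, so intention to treat is broken.** The article does not say so. It is silent on missing scores, and that rule may stand in an analysis plan that is not shown. If scores are imputed, nobody is lost. The conflict is therefore conditional.
- **That the repeated-measures ANOVA itself tests a pre-treatment difference.** It only mixes baseline into the group main effect. The explicit baseline comparison comes from hypothesis 2 and the 1-way ANOVA.
- **That the trial is underpowered.** The natural treatment test in a four-level design is group-by-time. At ρ = 0.5 its 80% is above the 77% of a single-visit comparison in completers, and at ρ = 0.7 it is close to the adjusted analysis (96% against 99.9%). The design is less efficient than it could be at almost no cost, but that does not make it inadequate.
- **That dropout follows burden.** This is not documented. The pilot's two withdrawals were for work and personal reasons, and Limitations cites fear of COVID-19.
- **That a known share could not reach T4.** Uniform accrual over the 730 days from December 2018 would give 204/730 = 28% counting six months from the end of the program, or 170/730 = 23% counting from baseline. Limitations reports a halt of several months, so uniform accrual is doubtful. The start of recruitment is also given variously as November 2018, December 2018 and January 2019, and the data-collection sentence closes a section mainly about recruitment and consent. It may not mark the last T4 visit.

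It is also fair to object that enrolment is complete and early results are already described, so a new model now is a late change.

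**Conclusion.** The point holds in this form. Baseline is written in as an outcome time and as a time at which the arms are expected to differ, which randomization makes meaningless. The cost is a main effect cut from 5.86 to 4.40 BDI points and power below that of a baseline-adjusted analysis in every scenario run. The gap is wide for the group main effect, and for group-by-time it ranges from wide at ρ = 0.3 to small at ρ = 0.7. The direction does not depend on the assumed correlation; the size does.

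The conflict with intention to treat is real for the method as named, but only if missing scores are not imputed. The dates are a separate inconsistency: both cannot be right if every recruit had a 6-month visit, and the documents do not allow the shortfall to be counted.

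**What to change.** 1. Make the comparison between arms a linear mixed model (MIXED, in the SPSS already named) on the T2–T4 scores of all randomized caregivers, analysed as randomized, with arm, visit, arm-by-visit and baseline score as covariate. Caregivers with no score after baseline add nothing to this model, so report their number by arm.
2. Delete the pre-intervention time from hypothesis 2 and show baseline scores by arm descriptively only.
3. Results states that analysis is at its final stage, and Anticipated Findings already describes early results. Declare the change as late and report the planned ANOVA next to the mixed model.
4. Reconcile the dates in Data Collection and Time Frame and in Approval. State the date of the last T4 visit and how many participants in each arm reached it.

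No new data are needed. The cost is wording, some syntax and a second set of results. The downside is small: a model changed after early results were seen carries less weight than one fixed beforehand, which is why both analyses should be shown.
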